### Study drug accountability, compliance and adherence

Patients will be asked to return any unused HTS 6% ampoules or carbocisteine at each study visit, to facilitate drug accountability. Adherence to HTS will be monitored utilising the eFlow nebuliser system with eTrack controller (which records data on nebuliser usage including frequency of use, dosage and maintenance). For the two HTS groups (intervention groups), study visit data from the eFlow nebuliser system with eTrack controller will be transferred to a Qualcomm Life 2Net Hub and subsequently to a secure Cloud-based platform. These data will not be reviewed and analysed until the end of the study, but will be checked weekly by a person not involved in study delivery, to ensure that the eFlow nebuliser system with eTrack controller is being used correctly and data are being transferred correctly.

### Outcomes

The primary outcome measure is the mean number of exacerbations over 52 weeks after randomisation. Secondary outcome measures are disease-specific HRQoL (respiratory symptoms of the domain of Quality of Life - Bronchiectasis (QoL-B) [29]), time to next exacerbation, number of days of antibiotics related to exacerbations, generic HRQoL (Euroqol 5 dimensions 5 levels (EQ-5D-5 L) [30]), measurement of health impairment using the St Georges Respiratory Questionnaire (SGRQ) [2]), health service use, quality-adjusted life years (QALYs), patient preferences for treatment, adverse events, lung function and adherence to trial treatment over 52 weeks.

#### Spirometry

All patients will be provided with a hand-held spirometer (*my*SpiroSense; PARI GmbH) to complete regular lung function tests at home (Additional file 3) and to record lung function at the beginning and end of an exacerbation. The *my*SpiroSense spirometer is a digital, self-calibrating instrument. Patients will bring the *my*SpiroSense to study visits so that its data can be imported to computers on site. The spirometry data can be viewed using the SpiroSense*Pro* software and additionally the database can be transformed and exported as a Microsoft Excel (.xls) file and viewed.

#### Exacerbation management

During the treatment period, if patients have symptoms of exacerbation for 48 h or feel that they require antibiotic therapy, they will be asked to call the study team. Exacerbations will be defined as per the recent consensus [31]. A comprehensive exacerbation management plan is detailed in Additional file 2. In general, patients will have rescue medication at home to facilitate management of exacerbations remotely. The trial will use an adjudication panel to categorise exacerbations.

#### Respiratory and Systemic Symptoms Questionnaire (RSSQ)

A member of the research team will administer the RSSQ questionnaire at each study visit to capture changes in the predefined signs and symptoms relative to normal day-to-day fluctuations [32]. It covers a range of patient-reported outcomes relating to cough, sputum, haemoptysis, dyspnoea, lethargy, sinuses, appetite and fever [33]. Modified versions of the RSSQ will be used to capture details of potential exacerbations reported between study visits.

#### Health-related quality of life (HRQoL) questionnaires

Three HRQoL questionnaires will be used: QoL-B, SGRQ and EQ-5D-5 L. The QoL-B assesses symptoms, functioning and HRQoL specific to patients with BE [29, 34, 35]. The SGRQ measures health impairment [2, 34]. The EQ-5D-5 L provides a simple descriptive profile and a single index value for health status [30].

#### Health Service Use Questionnaire

A questionnaire and log will be used to capture participants’ health service use over the study period, including details of medications prescribed (including antibiotics). This will be used for the health economic analysis.

#### Treatment Satisfaction Questionnaire for Medication

At each study visit, participants (except those randomised to the standard care group) will be asked what they think about the effectiveness, side effects and convenience experienced when using the medication over the last 2–3 weeks, or since they last used it. Patients assigned to the group combining HTS and carbocisteine (intervention group 3) will be asked to complete separate questionnaires for each treatment.

#### Schedule of assessments

All patients will be evaluated during the study according to the schedule of assessments outlined in Fig. 1 and Table 1. See also Additional file 8 for the SPIRIT checklist.

**Fig. 1 Fig1:**
[figure not shown]
Study schematic. BE, bronchiectasis; BRONCH-UK, UK Bronchiectasis Registry; EMBARC, European Multicentre Bronchiectasis Audit and Research Collaboration; NIHR, National Institute for Health Research; NICRN, Northern Ireland Clinical research Network; HTS, hypertonic saline; QoL-B, Quality of Life - Bronchiectasis; HRQoL, health-related quality of life; QALY, quality-adjusted life year; SGRQ, Saint George’s Respiratory Questionnaire

**Table 1 Tab1:**
[figure not shown]
Schedule of assessments

*It is planned that week 104 data will be collected from the European Multicentre Bronchiectasis Audit and Research Collaboration (EMBARC) or UK Bronchiectasis Registry (BRONCH-UK). If this is not possible, the participant will be asked to visit the research site for the data to be collected. BE, bronchiectasis; QoL-B, Quality of Life - Bronchiectasis; SGRQ, Saint George’s Respiratory Questionnaire; EQ-5D-5L, EuroQoL five dimension five level questionnaire

### Sample size

The required sample size is 380 patients including the internal pilot. Based on the primary outcome of mean exacerbations during 52 weeks and a pooled standard deviation of 0.9 exacerbations [36], and assuming the mean number of exacerbations in the control group is 0.7, 216 patients would be sufficient to detect a mean difference in exacerbation rate between groups of 0.4, with 90% power and at the 5% significance level. To allow for a potential interaction between the two interventions, 50% inflation has been included, requiring 324 patients. Further, compensating for 15% dropout gives the total required of 380 patients (95 in each of the four groups). In regard to secondary outcomes, this sample size would provide over 90% power to detect a minimally important difference of 8 points for the QoL-B scale (standard deviation of 18) at the 5% significance level [18, 29] and a 75% increase in median time to exacerbation at 98% power. It would also be sufficient to detect a medium effect size for the other secondary outcomes, at 95% power and 5% level of significance.

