### Study design

CLEAR is a multicentre, superiority, 2 × 2 factorial, randomized, open-label trial in BE with a 52-week follow-up period. Patients will be randomised (1:1:1:1 ratio) to one of four groups: HTS alone, carbocisteine alone, HTS and carbocisteine or standard care. Additionally, all patients will be followed up at 104 weeks to explore their mucoactive drug use in the 52 weeks following the completion of the main trial. For the SPIRIT checklist, please see Additional file 8.

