### Statistical analysis

Baseline characteristics, follow-up measurements and safety data will be described using descriptive summary measures depending on the scale of measurement. The primary analysis will be conducted on a modified intention-to-treat basis consisting of randomised participants with data from at least one post-baseline efficacy assessment. A per-protocol analysis may also be conducted to compare treatment groups. Groups will be compared for the primary outcome (number of exacerbations over 52 weeks) and antibiotic use (number of days of antibiotic use over 52 weeks) using negative binomial regression adjusted for baseline characteristics and other covariates. The QoL-B and other continuous outcomes will be compared between groups using analysis of covariance (ANCOVA) adjusting for baseline characteristics and other covariates. The trial’s 2 × 2 factorial design permits the separate testing of the effects of HTS and carbocisteine on HRQoL and the detection of any interaction between them. These tests will be implemented using three contrasts (representing HTS, carbocisteine and the interaction) in the models. For time to next exacerbation, Kaplan-Meier curves will be prepared and the log-rank test applied to compare the groups. Analyses will be two-sided and tested at an a priori significance level of *p* = 0.05. The primary time point has been defined as 52 weeks after randomisation. There is no adjustment for multiple testing at the different time points, because the primary outcome has been pre-defined and prioritised. Standard approaches will be used to detect missing data.

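### The 98% power quoted for time to exacerbation does not follow from the plan's own event rate and follow-up; under a constant hazard they give about 90–94%

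*Protocol article*

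**What the plan says.** The Sample size section builds the total from the primary outcome. It takes "a pooled standard deviation of 0.9 exacerbations" and, "assuming the mean number of exacerbations in the control group is 0.7", finds that "216 patients would be sufficient to detect a mean difference in exacerbation rate between groups of 0.4". For a possible interaction, "50% inflation has been included, requiring 324 patients", and an allowance for 15% dropout brings the total to 380, or 95 per group. It then says that this sample size also gives adequate power for secondary outcomes, among them "a 75% increase in median time to exacerbation at 98% power". No control median, event proportion, event count or hazard shape accompanies that clause.

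Study design describes a "randomized, open-label trial in BE with a 52-week follow-up period" with equal allocation to four groups. Statistical analysis compares time to next exacerbation by Kaplan-Meier curves and a log-rank test, and adds: "Analyses will be two-sided and tested at an a priori significance level of" 0.05.

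**The concern.** The power of a log-rank test depends on the number of first events, not on the number of patients. A control mean of 0.7 exacerbations per year implies that roughly half of the controls, and fewer treated patients, have any exacerbation in 52 weeks. The event count is then well below the number randomised, and 98% looks too high.

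At stake is the accuracy of one stated power figure. A reader would take the chance of missing the target effect to be 2%, whereas the section's own inputs put it at about 6–10%. A non-significant result on this outcome would be read as stronger evidence against the effect than the design supports.

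**Working it through.** **Inputs.** From Sample size: control rate 0.7 per 52 weeks, SD 0.9, median ratio 1.75, 216, 324 and 380 patients, 15% dropout. From Study design: 52 weeks, 1:1:1:1 allocation, hence 1:1 at each factorial margin (162 vs 162, or 190 vs 190). From Statistical analysis: log-rank test, two-sided 5%. Assumption added here: constant hazard, with only the drug being tested active.

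**Step 1. Trying to reproduce 98%.** Schoenfeld's formula is power = Φ(√D/2 × |ln HR| − 1.96), where D is the number of first events. With constant hazard HR = 1/1.75 = 0.571 and |ln HR| = 0.560. If all 216 patients of the uninflated calculation had an event, D = 216 and power is 98.4% (98.0% by Freedman's formula). That matches the stated figure, but it uses neither the planned sample size nor any censoring. It is a possible origin, not an established one.

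**Step 2. Events needed for 98%.** D = 4 × (1.96 + 2.054)² / 0.560² ≈ 206 (Freedman: 217).

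**Step 3. Event proportions at 0.7 per year.**
- Control: 1 − exp(−0.7) = 0.503.
- Treated: rate 0.7/1.75 = 0.4, so 1 − exp(−0.4) = 0.330.

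With 15% dropout through the year, the dropout hazard is d = −ln 0.85 = 0.163 and the event proportion is λ/(λ+d) × [1 − exp(−(λ+d))], which gives 0.469 and 0.306.

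**Step 4. Events and power.**

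| Sample | First events | Schoenfeld | Freedman | Log-rank simulation (10,000 runs) |
|---|---|---|---|---|
| 324 evaluable | 162 × (0.503 + 0.330) = 135 | 90.2% | 88.7% | 90.4% |
| 380, 15% dropout through the year | 190 × (0.469 + 0.306) = 147 | 92.4% | 91.1% | 92.1% |
| 380, all followed | 190 × (0.503 + 0.330) = 158 | 94.1% | 92.9% | 93.8% |

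**Step 5. Overdispersion.** The SD of 0.9 gives a variance of 0.81, above the mean of 0.7. A negative binomial count with dispersion (0.81 − 0.7)/0.7² = 0.22 lowers the event proportions to 0.478 and 0.318. With 324 patients that is 129 events and 88.8% power.

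**Step 6. Control rate that would give 98%.** Solving n × [2 − exp(−λ) − exp(−λ/1.75)] for 206 to 217 events gives λ = 1.34–1.47 per year with 162 per arm, and 1.02–1.11 with 190 per arm and no dropout. Overall this is about 1.0–1.5, against the stated 0.7.

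**Step 7. Medians at 0.7 per year.** Control: ln 2/0.7 × 52 = 51.5 weeks. Treated: 51.5 × 1.75 = 90.1 weeks. At week 52, exp(−0.4) = 67% of treated patients are still event-free.

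**The case against.** **Hazard shape.** The strongest defence is that constant hazard is not in the document; it is supplied here. If first-event times follow a Weibull distribution with the control cumulative hazard kept at 0.7 over 52 weeks, a median ratio of 1.75 corresponds to HR = 1.75^(−k) for shape k. At k = 1.25 the hazard ratio is 0.497, and 324 patients give 129 events and 97.8% power. At k = 1.2, 380 patients with 15% dropout give 97.9%. This stands: 98% is not impossible, and a reader who concludes that it is unattainable goes too far. But the section states no rising hazard, and its SD of 0.9, with variance above the mean, points mildly the other way. A falling hazard (k = 0.85) would cut power to 80% with 324.

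**A different rate.** The time-to-event calculation may have used a higher control rate given only in the full protocol. That is possible, but it would sit beside 0.7 in the same paragraph and need reconciling. For the same reason one cannot say that 98% arises only when all 216 patients have an event.

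**Which sample size.** The clause refers to the whole sample, and a log-rank test uses dropouts' follow-up until censoring. So 90% is the low end, and about 92% is the fairer central figure.

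**The median.** A reader might infer that the trial has chosen an effect measure it cannot estimate. The documents do not support that: the median ratio appears only as a design target, and a log-rank test does not require either median to be reached.

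**Other comparisons.** Power is lower if both drugs work (83.8% with 324) or for one arm against standard care (63% with 81 vs 81). The section does not claim power for those cases, so they are no evidence that its figure is wrong.

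**Conclusion.** The point holds in a limited form. From the plan's own control rate, follow-up and test, and a constant hazard, power for a 75% longer median is about 90–94% at each factorial margin, on about 135–158 first events, against about 206 needed for the stated 98%. The shortfall is 4–8 percentage points.

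The conclusion rests on a constant hazard, on 0.7 per year applying to first events, and on the other drug having no effect. A control rate of about 1.0–1.5 per year or a moderately rising hazard would restore 98%; the first contradicts the section and the second is not stated in it.

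This is a secondary outcome. The total of 380 comes entirely from the primary outcome and is unaffected, and power remains around 90% or better in the base case. It is a figure to correct, not a flaw in the design.

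**What to change.** In Sample size, replace the clause with a statement that the sample gives about 90–94% power (about 92% with 380 randomised and 15% dropout) for a hazard ratio of 0.57 at each factorial margin, on about 135–158 expected first events, assuming a constant hazard at the stated control rate. If a different control rate or hazard shape lay behind 98%, state it and reconcile it with 0.7.

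Express the target as a hazard ratio instead of a median ratio, because at 0.7 per year the treated median of about 90 weeks falls beyond the 52-week follow-up.

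The cost is wording only, with a slightly less favourable secondary power figure. No extra patients and no change to the analysis are needed.

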### Recruitment

Potential participants may be identified through the EMBARC and BRONCH-UK registries at each of the participating sites, through referrals or while in clinics. Twitter and Facebook accounts (https://twitter.com/TrialCLEAR; https://www.facebook.com/TrialCLEAR/) are being used to encourage engagement and awareness of the trial. The study team will have regular teleconferences with sites to review screening and recruitment figures and resolve any issues.

### Randomisation and blinding

Treatment allocation at each site will be assigned using a concealed automated randomisation process provided by an external organisation. Participants who give their consent will be allocated using a fixed block size to one of the four groups (three intervention groups or one standard care group) in a 1:1:1:1 ratio using a central randomisation system. Randomisation will be stratified by (1) site, (2) exacerbations in the last year (2–3 times, > 3 times) (to minimise baseline imbalances in antibiotic use) and (3) current use of macrolides (yes, no). The trial is open label, and patients, investigators and outcome assessors will be aware of treatment allocation.

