## Methods/design

### Study setting

The CLEAR sites will include at least 16 National Health Service (NHS) hospitals in the UK with access to patients with BE managed according to BTS guidelines. Sites will include those that are part of the BRONCH-UK/or EMBARC research network [28], and additional sites will be chosen from the Northern Ireland Clinical research Network (NICRN)/National Institute for Health Research Clinical Research Network (NIHR CRN) portfolio if required. The current list of study sites is in Additional file 5.

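### A constant block size within site-level strata weakens allocation concealment in this open-label trial, to a degree set by the undisclosed block size

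*Protocol article*

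**What the plan says.** All the relevant statements are in the protocol article, nearly all of them under Randomisation and blinding. Participants "will be allocated using a fixed block size to one of the four groups", "in a 1:1:1:1 ratio using a central randomisation system". The size of the block is not stated.

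On strata, "Randomisation will be stratified by (1) site, (2) exacerbations in the last year (2–3 times, > 3 times"), and the third factor is "3) current use of macrolides (yes, no"). That makes four strata at each site. Under Study setting, "The CLEAR sites will include at least 16 National Health Service (NHS) hospitals in the UK", so there are at least 64 strata.

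On concealment, treatment is "assigned using a concealed automated randomisation process provided by an external organisation". On blinding, "The trial is open label, and patients, investigators and outcome assessors will be aware of treatment allocation".

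**The concern.** Permuted blocks of constant length leave a pattern. Once a few allocations in a stratum are known, some groups become less likely or impossible for the next patient, and the last patient of each block is fully determined. Here staff see every past allocation, and they know each patient's stratum because exacerbation history and macrolide use are clinical facts they hold. A 1:1:1:1 ratio makes the block a multiple of 4, so there are few lengths to test against the observed sequence. Concealing the list centrally does not prevent that deduction.

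What is at stake is selection at enrolment. Patients come from clinics, referrals and registries (Recruitment), so the timing of enrolment is partly discretionary. The groups differ a good deal in burden, from twice-daily nebulisation to no added drug (Intervention and comparator). A recruiter who suspects which group is next could bring a patient forward or hold one back. With no blinding after allocation, unpredictable allocation is one of the main safeguards left. The Discussion itself defends the open-label design by pointing to rigour elsewhere in trial delivery.

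**Working it through.** The article gives no figure for predictability, so there is none to reproduce. The question is how much an observer can deduce.

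**Inputs from the article.** 380 patients (Sample size); at least 16 sites (Study setting); 2 × 2 = 4 strata per site, four groups in equal ratio, and a fixed block (Randomisation and blinding). Average stratum at 16 sites: 380 / (16 × 4) = 5.9, taken as 6. More sites would make it smaller; a large site's common stratum would be bigger.

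**Assumptions.** Blocks run separately within each stratum, which is the natural reading. Sizes 4, 8 and 12 are tried because the true size is not given. The observer knows the block size and all earlier allocations in the stratum. This is the most favourable case for prediction.

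**Method.** At each position the best guess is the group with the most places left in the block. Its chance of being right is (places left for that group) / (places left in the block), averaged over all possible histories. An allocation is certain when only one group has places left.

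**Stratum of 6, by position:**
- Block 4: 1/4, 1/3, 1/2, 1, 1/4, 1/3. The sum is 2.667, and 2.667/6 = 44%. One of the six (the fourth) is certain: 1/6 = 17%.
- Block 8: 0.250, 0.286, 0.333, 0.400, 0.443, 0.476. The sum is 2.188, and 2.188/6 = 36%. None is certain, because the block is not completed.
- Block 12: 0.250, 0.273, 0.300, 0.333, 0.355, 0.370. The sum is 1.881, and 1.881/6 = 31%. None is certain.

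**Stratum of 24, certain share:**
- Block 4: 6 of 24 = 25%.
- Block 8: the last place is always certain, and the seventh is certain when the last two places belong to the same group, with probability 4/28 = 1/7. So 3 × (1 + 1/7) / 24 = 14%.
- Block 12: 2 × (1 + 12/66 + 4/220) / 24 = 10%.

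**Whole trial.** Simulation spread 380 patients over 64 strata, equally or with assumed unequal shares, so that some strata complete their blocks and others do not:

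| Block | Certain | Best guess right |
|---|---|---|
| 4 | about 19% | about 47% |
| 8 | 5–7% | 39–40% |
| 12 | 0.4–3% | 33–36% |

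**Does varying the size help?** The next table gives certain share / best guess right. The observer is assumed to know the candidate sizes of the mix. Mixes are simulated with the two sizes equally likely.

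| Stratum | Fixed 4 | Fixed 8 | Fixed 12 | Mix 4 and 8 | Mix 8 and 12 |
|---|---|---|---|---|---|
| 6 | 17% / 44% | 0% / 36% | 0% / 31% | 0% / 40% | 0% / 34% |
| 12 | 25% / 52% | 10% / 42% | 10% / 44% | 6% / 47% | 4% / 43% |
| 24 | 25% / 52% | 14% / 47% | 10% / 44% | 7% / 48% | 4% / 44% |

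A mix of 4 and 8 clearly improves on a fixed 4. Against a fixed 8 or 12 it lowers certainty in the longer strata but makes guessing easier on average. A mix of 8 and 12 improves on a fixed 8 in strata of 6 and 24. In strata of 12 it more than halves the certain share while average guessing is about the same (43% against 42%).

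**The case against.** The block size is not published and may be withheld from sites; that detail belongs in the randomisation specification, which is not shown. Staff would have to follow four sequences per site, each averaging about 6 patients. If the block is 8 or 12, most strata would complete few blocks and almost nothing would be certain. All of this stands and limits the size of the problem. It does not remove it, since a fixed length can be inferred from open allocations and guessing beat chance at every size tried.

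The analysis also gives some protection. Prior exacerbations and macrolide use are stratification factors, so steering could act only within their levels. The negative binomial model adjusts for baseline characteristics and other covariates (Statistical analysis). That deals with part of any measured imbalance, but not with selection on prognosis that nobody recorded.

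Three stronger readings are tempting, and the article does not support them:
- That staff can simply foresee allocations and concealment has failed. Most allocations remain uncertain even with a block of 4, and nothing shows that prediction took place.
- That about a quarter of all allocations would be certain and half guessable. Those figures (25% and 52%) need a block of 4 and completed blocks throughout.
- That a patient-reported primary outcome makes matters worse. Patients start the report, but exacerbations follow a consensus definition and an adjudication panel categorises them (Exacerbation management). In any case, outcome reporting raises a question of detection bias, separate from selection at enrolment.

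**Conclusion.** The point holds as a weakness in a stated design choice. A constant block length, site-level strata and visible allocations together make some late-block allocations deducible, and central concealment does not prevent it. In a typical stratum of 6 the certain share is 17% if the block is 4 and zero if it is 8 or 12. The best guess is right 44%, 36% or 31% of the time, against 25% by chance. In strata of 24 the certain share is 25%, 14% or 10%.

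These figures rest on assumed block sizes and on an observer who knows the size and tracks each stratum, so real predictability would be lower wherever staff do neither. The risk is avoidable and cheap to reduce, and the change should be made. The documents give no evidence that bias has occurred.

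**What to change.** For blocks not yet opened, have the central system draw block sizes at random. Choose them with knowledge of the present size so that on average they are no smaller than it: for example 4 and 8 if the present block is 4, or 8 and 12 if it is 8. Withhold the sizes from sites until recruitment ends, and state in the protocol that the size varies, without giving the values.

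At the December 2019 status report 130 patients had been recruited, so 380 − 130 = 250 allocations were still to come, apart from those in blocks already open. Allocations already made cannot be changed.

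The cost is regenerating the unused part of the list and slightly more imbalance from incomplete blocks within strata. The sample size stays at 380.

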## Discussion

CLEAR is a pragmatic effectiveness trial. It was designed as an open-label trial (in preference to a blinded trial) because of factors including the prohibitive cost and feasibility of conducting a trial with blinded patients, practitioners and/or outcome assessors. There is increasing support for trials to use more pragmatic research designs [37], especially in therapy trials where blinding is not feasible [38] or practical and when the funding required to implement blinded trials could be better used to optimise rigour in other areas of trial delivery (Anand R, Norrie J, Bradley JM, McAuley DF, Clarke M: Fool’s gold? Why double blind trials are not always best, submitted). The CLEAR trial also has added value through the embedding of low-cost sub-studies to resolve important uncertainties about trial methods [27].

The findings of the CLEAR trial will be published in a peer-reviewed journal and will help inform national and international guidelines on the use of HTS and carbocisteine as mucoactive drugs for treatment of BE. A lay person’s summary will be sent to local and national patient support and liaison groups, including the European Lung Foundation BE Patient Advisory Group and the British Lung Foundation as well as similar organisations in devolved nations of the UK. A report of the study findings will be provided for the INVOLVE registry. Following journal publication, key findings will be posted on institutional websites that are freely available to the general public and others.

In summary, HTS and carbocisteine are the two most commonly used mucoactive agents in BE, being prescribed to up to 20% of patients but without a solid evidence-base for their effectiveness. The CLEAR trial will demonstrate whether these one-in-five patients with BE are being asked to take burdensome medications that are ineffective or, if effective, whether more consideration needs to be given to prescribing these medications to the remaining 80% of patients with BE.

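### As written, nothing shields the exacerbation adjudication panel from treatment allocation, although it categorises the events on which the primary outcome rests

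*Protocol article*

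**What the plan says.** Four parts of the protocol article bear on this point.

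- **Outcomes:** "The primary outcome measure is the mean number of exacerbations over 52 weeks after randomisation".
- **Exacerbation management** and the **RSSQ** section: an event comes to notice through the patient. Patients with symptoms for 48 hours, "or feel that they require antibiotic therapy, they will be asked to call the study team". The details are then taken on a symptom questionnaire: "Modified versions of the RSSQ will be used to capture details of potential exacerbations reported between study visits". After that, "The trial will use an adjudication panel to categorise exacerbations".
- **Randomisation and blinding:** "The trial is open label, and patients, investigators and outcome assessors will be aware of treatment allocation".
- **Discussion:** the open-label design is attributed to factors including "the prohibitive cost and feasibility of conducting a trial with blinded patients, practitioners and/or outcome assessors".

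The article does not say that the panel is masked or that its case material has the allocation removed. The remark under Data collection that patient data will be anonymised concerns identity, not treatment group.

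**The concern.** An exacerbation here begins with how a patient feels and whether that patient calls. In an open-label trial this step cannot be blinded. Deciding afterwards whether a reported episode counts, or how it is categorised, involves judgement in borderline cases, and a panel working from records is a step where knowledge of the arm can be removed. If the panel knows the arm, borderline episodes could be accepted more readily in patients without a study drug, which would favour the drugs. Time to next exacerbation, antibiotic days related to exacerbations and cost per exacerbation avoided rest on the same events.

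**Working it through.** **Reading the sections together.** The primary outcome is a count of exacerbations. A panel categorises exacerbations. A body that categorises outcome events is assessing the outcome, so by function it falls under the assessors who will know the allocation, and the sentence excepts nobody. This is an inference, because the panel is not named in that sentence. The Discussion does name outcome assessors in its cost argument. That argument concerns running a blinded trial, whereas the panel already exists. Giving it records without the arm does not require blinding patients or practitioners.

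**The plan's own figures.** Inputs from Sample size: "a pooled standard deviation of 0.9 exacerbations", "assuming the mean number of exacerbations in the control group is 0.7", difference 0.4, 90% power, 5% significance level (two-sided, per Statistical analysis).

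- Per group, normal approximation: 2 × (1.960 + 1.282)² × 0.9² / 0.4² = 106.4, so 107. The t-test version gives 107.36, so 108 per group and 216 in total, as stated.
- 216 × 1.5 = 324, as stated. 324 / 0.85 = 381.2, against the stated 380.

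The sample size is not in dispute; it supplies inputs for the illustration.

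**Illustration of size.** From the article: 324 / 2 = 162 patients per margin (drug against no drug) and a mean of 0.7. Assumed, not in the documents:

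- no true effect of either drug;
- 0.7 candidate events per patient in every group (the article gives 0.7 as the control mean, not as a rate before adjudication);
- the acceptance rates below;
- a panel decision that settles whether an event is counted.

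Candidate events per margin: 0.7 × 162 = 113.4.

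*Case A: 90% accepted in standard care only, 80% in the three drug groups.* Half of each no-drug margin takes the other drug, so that margin accepts (90 + 80) / 2 = 85%, and the drug margin accepts 80%.

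- Rate ratio: 0.80 / 0.85 = 0.94.
- Events: 113.4 × 0.85 − 113.4 × 0.80 = 96.4 − 90.7 = 5.7, about 6.
- Shift in mean: 0.7 × 0.05 = 0.035.

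*Case B: 90% accepted across the whole no-drug margin, 80% across the drug margin.*

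- Rate ratio: 0.80 / 0.90 = 0.89.
- Events: 113.4 × 0.90 − 113.4 × 0.80 = 102.1 − 90.7 = 11.3, about 11.
- Shift in mean: 0.7 × 0.10 = 0.07.

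**Effect on false positives.** Standard error of the difference: 0.9 × √(2/162) = 0.10. Two-sided type I error: Φ(−1.96 + shift/SE) + Φ(−1.96 − shift/SE). This is a normal approximation with the SD held at 0.9, not the planned negative binomial model.

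| Difference in acceptance between margins | Shift in mean | Type I error |
|---|---|---|
| 0 points | 0 | 0.050 |
| 5 points (Case A) | 0.035 | 0.064 |
| 10 points (Case B) | 0.07 | 0.108 |
| 20 points | 0.14 | 0.288 |

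Leniency confined to standard care has to be twice as large as the margin difference shown: a 20-point gap there gives the 10-point row.

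**The case against.** The strongest reply is that the article never says the panel is unmasked. The panel appears in a different section from the awareness statement, and the assessors could be the site staff who administer the questionnaire. The exacerbation management plan (Additional file 2), the full protocol and any panel charter are not shown, and operational detail of this kind commonly sits there. This stands as far as it goes: a reader might infer that the article declares the panel unblinded, and the text does not support that. It does not dispose of the point, because the awareness statement is affirmative and unqualified, not silent. If another document masks the panel, the statement is too broad and needs correcting.

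Three further objections have force.

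- The Discussion does include assessors in its cost argument, so it cannot be read as covering only patients and site staff. Unblinded assessment is a disclosed choice with a stated reason. What is missing is why that reason reaches a panel working from records.
- The article says the panel categorises events. It does not say that its decision sets the primary count. A reader might assume so, but the illustration above needs it as an assumption.
- A consensus definition and a structured questionnaire limit discretion for any assessor, so adjudication is not the only protection.

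A reader might also take 0.89, or 11 events, as the natural size of the bias. That requires a gap across a whole margin, in which half the no-drug patients take the other study drug. Leniency towards patients on no study drug gives only Case A.

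**Conclusion.** The point holds in a limited form. Followed as written, the article allows exacerbations to be categorised with knowledge of the arm, and it gives no reason specific to the panel for allowing this. It does not establish that the panel is in fact unmasked, that its decision fixes the primary count, or that any bias must favour the drugs; that direction is plausible, not shown.

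If acceptance differs by 10 points between standard care and the drug groups, the spurious marginal rate ratio is about 0.94 and the type I error about 0.064. If the same gap runs across a whole margin, the figures are 0.89 and about 0.11. All of these rest on assumed acceptance rates. The change is worth making because it is cheap and protects the primary outcome, not because a bias of known size has been shown.

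**What to change.** State under Exacerbation management that the panel classifies events from records with allocation and treatment clues removed: arm, nebuliser and eTrack data, carbocisteine, drug accountability and treatment satisfaction data. In Randomisation and blinding, limit the awareness statement to patients, investigators and site outcome assessors. If a charter or additional file already masks the panel, correct that statement to say so. If masking is not possible, give the reason specific to the panel.

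The panel already exists, so the cost is charter wording and a little redaction work. Some records will still reveal the arm by accident. Masking would limit bias in classification only; patients' decisions to report symptoms or call would still be made with knowledge of treatment.
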